### Evaluation criteria and judgment of curative effect

2.6

1.Main outcome indicators: TCM syndrome score (refer to the guiding principles of Clinical Research of New drugs of traditional Chinese Medicine^[15]^), N-terminal pro-brain natriuretic peptide (NT-pro BNP), left ventricular ejection fraction, brain natriuretic peptide (BNP).2.Secondary outcome indicators: stroke volume (SV), left ventricular end-systolic diameter, left ventricular end-diastolic diameter.3.Adverse reactions: including abnormal liver function and uncomfortable symptoms (such as dizziness, nausea, etc) during treatment.

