**Methods::**

This is a prospective randomized controlled trial to study the efficacy and safety of Shenfu injection combined with sodium nitroprusside in the treatment of chronic heart failure in patients with coronary heart disease. The patients will be randomly divided into a treatment group and the control group according to 1:1, in which the treatment group is treated with Shenfu injection combined with sodium nitroprusside, and the control group is treated with sodium nitroprusside alone. Both groups will be treated with standard treatment for 7 days and followed up for 30 days to pay attention to their efficacy and safety indexes. The observation indexes include TCM syndrome score, N-terminal pro-brain natriuretic peptide, left ventricular ejection fraction, brain natriuretic peptide, left ventricular end-systolic diameter, left ventricular end-diastolic diameter, stroke volume, adverse reactions and so on. We will use SPSS 25.0 software for data analysis.

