### Sample size calculation

2.4

This study was a pilot clinical trial. According to the analysis and calculation of the related literature published in the past 10 years, the therapeutic efficiency of Western medicine is 72.3%, and the effective rate of traditional Chinese medicine combined with Western medicine is 92.1%. Using the sample size estimation formula compared with multiple sample rates, set the significance test level α = 0.05, then μ_α_ = 1.96, 1−β = 0.9, μ_β_ = 1.28. δ = π_1_−π_2_ sample size estimation formula for comparison of 2 sample rates:$$N_{1}=N_{2}={\left(\frac{\mu_{\alpha }+\mu_{\beta }}{\delta }\right)}^{2}[\pi_{1}(1-\pi_{1})+\pi_{2}(1-\pi_{2})]$$

The sample size of each group is calculated to be 73. Considering shedding and other factors, the expansion is about 20%, and it is calculated that 182 patients need to be included. According to the simple randomized method, the patients included in the study are divided into control group (n = 91) and the observation group (n = 91).

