### Data collection and management

2.7

The data are collected according to the evaluation criteria before the beginning of treatment, 72 hours after the treatment and at the end of treatment. Thirty days after the end of treatment, each patient is followed up by outpatient or telephone. The reasons for the loss of follow-up cannot be collected. All data will be collected jointly by 1 or 2 assistants. Personal information about potential participants and registered participants will be collected, shared, and stored in a separate storeroom to protect before, during, and after confidentiality. The access to the database is limited to the researchers of this research group.

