### Statistical analysis

2.8

In this study, SPSS25.0 statistical analysis software is used for data analysis, and the measurement data are expressed by ($\bar{\text{x}}\pm \text{S}$). For the data that accord with normality and homogeneity of variance, group *t* test is used between groups, paired *t* test is used within groups, rank sum test is used for those who do not conform to normal distribution, and *χ*^2^ test is used for counting data. When *P* *<* 0.05, it is statistically significant.

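### Four equal main outcomes, two post-baseline assessments and one unadjusted P < 0.05 rule, with no primary outcome, primary time or success rule, so the 5% error level used for sizing is not protected

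*Protocol article*

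**What the plan says.** Section 2.6 of the protocol article begins "Main outcome indicators: TCM syndrome score" and continues with NT-proBNP, LVEF and BNP. These four form the top tier. Stroke volume and the two ventricular diameters are secondary. Nothing ranks the four among themselves.

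Section 2.7 collects the data "before the beginning of treatment, 72 hours after the treatment and at the end of treatment", which gives two assessments after baseline. Section 2.5 speaks only of evaluation before and after treatment and does not choose between them.

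Section 2.8 gives the tests (t test, rank sum test, chi-squared test) and one threshold for all of them: at P < 0.05, "it is statistically significant".

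Section 2.4 sizes the trial on a comparison of two rates. It says to "set the significance test level α = 0.05", uses "1−β = 0.9, μ_β_ = 1.28", and assumes that "the therapeutic efficiency of Western medicine is 72.3"% and "the effective rate of traditional Chinese medicine combined with Western medicine is 92.1"%. The abstract gives the allocation: patients are "randomly divided into a treatment group and the control group according to 1:1".

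**The concern.** The nominal 5% error and the 90% power in section 2.4 describe one test. The plan then places four outcomes at its top level, observes them twice after baseline and judges every comparison at the same unadjusted threshold. It does not say which result decides the trial. A report could therefore rest its efficacy conclusion on whichever main outcome and visit fell below 0.05 and still cite an alpha of 0.05.

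The sample size does not settle the matter by implication. It is built on an effective rate, and no such rate appears among the main or secondary outcomes in section 2.6. The one test that carries the planned error rate and power is thus not a listed test, and the listed tests have no joint error control.

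**Working it through.** **1. The plan's own figure.** Inputs from section 2.4: π₁ = 0.723, π₂ = 0.921, δ = 0.198 in absolute value, z values 1.96 and 1.28.

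- ((1.96 + 1.28)/0.198)² = 267.77
- 0.723 × 0.277 + 0.921 × 0.079 = 0.2003 + 0.0728 = 0.2730
- 267.77 × 0.2730 = 73.1 per group, against the stated 73
- 73/0.80 = 91.25, against the stated 91 per group and 182 in total

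The figure reproduces. The value 1.96 shows a two-sided 0.05 spent on a single comparison.

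**2. Number of comparisons.** Four main outcomes (section 2.6) at one visit make four between-group tests. At both post-baseline assessments (section 2.7) they make eight. Within-group tests and secondary outcomes are left out.

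**3. Independent tests, no true effect.** The chance of at least one two-sided P < 0.05 is 1 − 0.95^k.

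- k = 4: 1 − 0.8145 = 18.5%
- k = 8: 1 − 0.6634 = 33.7%

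For results favouring Shenfu only, it is 1 − 0.975^k.

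- k = 4: 1 − 0.9037 = 9.6%
- k = 8: 1 − 0.8167 = 18.3%

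**4. Correlated tests.** The document gives no correlations, so a common correlation ρ between all test statistics is assumed, from 0.3 to 0.7. With φ and Φ the standard normal density and distribution function, the chance of at least one two-sided false positive is

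1 − ∫ φ(u) [Φ((1.96 − √ρ·u)/√(1−ρ)) − Φ((−1.96 − √ρ·u)/√(1−ρ))]^k du.

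For favourable results only, the second Φ is dropped.

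| Tests | ρ (assumed) | Any two-sided P < 0.05 | Favouring Shenfu only |
|---|---|---|---|
| 4 | 0 | 18.5% | 9.6% |
| 4 | 0.3 | 17.4% | 8.7% |
| 4 | 0.5 | 15.6% | 7.8% |
| 4 | 0.7 | 13.0% | 6.5% |
| 8 | 0 | 33.7% | 18.3% |
| 8 | 0.3 | 30.0% | 15.2% |
| 8 | 0.5 | 25.0% | 12.5% |
| 8 | 0.7 | 19.1% | 9.5% |

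The reference is 5% for the two-sided column and 2.5% for the last column.

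**5. A less regular pattern.** Assume NT-proBNP and BNP correlate at 0.7 to 0.9, other outcome pairs at 0.2 to 0.4, and visits at 0.5 to 0.8. Simulation then gives 14.8 to 17.0% for four tests and 22.4 to 29.1% for eight, inside the ranges above.

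**6. If all four had to succeed.** There would be no inflation, but power would fall. As an illustration, four independent tests with an assumed 90% power each would all succeed with probability 0.9⁴ = 66%. Section 2.4 makes no allowance for this.

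**The case against.** Several points on the other side carry weight.

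- **No success rule is stated.** Section 2.8 says when a test is significant. It does not say that one significant main outcome establishes efficacy. This stands: the inflation depends on an any-one reading, and the defect in the text is that the rule is undefined.
- **The eight-test count is less secure than the four-test count.** Section 2.7 describes data collection and gives the 72-hour values no confirmatory role. This stands too. The firm part is the four equal main outcomes.
- **An analysis plan that is not shown may handle multiplicity.** It may. But the protocol article itself fixes four main outcomes and one threshold for everything, and an analysis plan would have to depart from that.
- **Section 2.4 calls the trial a pilot.** The trial is nevertheless sized for 90% power, and the Discussion gives its purpose as verifying that Shenfu improves symptoms and cardiac function. The label does not remove the problem.

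Two stronger readings are tempting. One is that a false efficacy claim is three to six times likelier than 5%. That mixes scales: the multiple counts significance in either direction, while an efficacy claim needs a favourable result. Against 5%, favourable results alone come to 6.5/5 = 1.3 up to 18.3/5 = 3.7 times. The multiple also depends on correlations that the document does not give. The other reading is that BNP merely repeats NT-proBNP and so makes matters worse. The document says nothing about their overlap, and a near-duplicate adds little: with that pair at 0.9 and the rest at 0.3, the four-test figure is about 15%, below the 17.4% with all pairs at 0.3.

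**Conclusion.** The point holds: as written, the plan does not protect the 5% level on which it was sized, because it fixes four co-equal main outcomes under one unadjusted threshold and leaves the deciding outcome, time and success rule open.

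The size is conditional on any single significant main outcome being read as efficacy. At one visit, the two-sided false-positive chance is then 18.5% under independence and about 13 to 17% at assumed equal correlations of 0.7 to 0.3. It reaches 34%, or about 19 to 30%, only if both visits count. In the direction of benefit, the range is 6.5 to 9.6% or 9.5 to 18.3%, against 2.5%.

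The documents support neither a fixed multiple of 5% for efficacy claims nor the view that the authors intend to pick among eight results. The mismatch with the effective rate in section 2.4 needs no assumption.

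**What to change.** In sections 2.6 and 2.8, make end of treatment the primary time. Test the four main outcomes there by Holm at overall two-sided 0.05, with ordered P values compared with 0.05/4 = 0.0125, 0.05/3 = 0.0167, 0.05/2 = 0.025 and 0.05. Declare the 72-hour values supportive, with no efficacy claim.

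Alternatively, the sponsor names one primary outcome at end of treatment, tested at 0.05, and tests the other three main outcomes as secondary, in a fixed order or by Holm. The choice of outcome is the sponsor's; the document gives no ground for preferring one.

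In either case, section 2.4 must be brought into line: base the sample size on the chosen endpoint or endpoints, or state that 182 was derived from a different one.

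The text change is short, and no visit or measurement changes. The price is a stricter threshold for each main outcome under Holm, or loss of stand-alone claim status for three of them. As a guide to the first, the plan's own formula at 0.0125 (z = 2.498, with 1.28 for power) gives ((2.498 + 1.28)/0.198)² × 0.2730 ≈ 99 per group before dropout instead of 73. That illustrates the cost on the effective rate only; the listed outcomes need their own assumptions.

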### Data collection and management

2.7

The data are collected according to the evaluation criteria before the beginning of treatment, 72 hours after the treatment and at the end of treatment. Thirty days after the end of treatment, each patient is followed up by outpatient or telephone. The reasons for the loss of follow-up cannot be collected. All data will be collected jointly by 1 or 2 assistants. Personal information about potential participants and registered participants will be collected, shared, and stored in a separate storeroom to protect before, during, and after confidentiality. The access to the database is limited to the researchers of this research group.

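### Between-arm tests of the continuous outcomes use one time point and no baseline, although baseline, 72-hour and end-of-treatment values are collected; a baseline-adjusted repeated-measures model would be more precise at almost no cost

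*Protocol article*

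**What the plan says.** Section 2.7 (Data collection and management) sets three measurement times: before treatment, "72 hours after the treatment and at the end of treatment". The continuous outcomes in section 2.6 include the TCM syndrome score, NT-pro BNP, BNP and ejection fraction as main outcomes, and stroke volume and two ventricular diameters as secondary ones. No time point is attached to any of them.

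For measurement data that are normal with equal variances, section 2.8 (Statistical analysis) says that a group t "test is used between groups". Paired t tests are kept for changes within an arm, and rank-sum tests for non-normal data. No baseline covariate and no repeated-measures model is named.

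On loss, section 2.4 states: "Considering shedding and other factors, the expansion is about 20" per cent. Section 2.7, directly after the sentence on the contact 30 days after treatment, adds: "The reasons for the loss of follow-up cannot be collected". Neither section says when patients are expected to be lost.

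**The concern.** A two-sample t or rank-sum test uses one value per patient. When the arms are compared at end of treatment, the test uses neither the baseline nor the 72-hour value, and a patient without the final value cannot enter it. The paired tests within arms use baseline, but they do not compare the arms.

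Two things are at stake. The first is precision. Natriuretic peptides, ejection fraction and symptom scores usually correlate with their own baseline, so an unadjusted comparison leaves explainable variation in the error term. The second is bias, and it is conditional. If some patients leave between 72 hours and day 7, and leaving is related to how they were doing, a comparison of those who remain can be distorted. The 72-hour value would then be the best available information on those who left.

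**Working it through.** **The plan's own figures.** Section 2.4 gives these inputs: "set the significance test level α = 0.05" (quantile 1.96), power 0.9 (quantile 1.28), and "the therapeutic efficiency of Western medicine is 72.3%, and the effective rate of traditional Chinese medicine combined with Western medicine is 92.1" per cent.

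- n = ((1.96 + 1.28)/0.198)² × [0.723 × 0.277 + 0.921 × 0.079] = 267.8 × 0.2730 = 73.1. The plan says: "The sample size of each group is calculated to be 73".
- 73/0.8 = 91.25, taken as 91 per group. The plan says: "it is calculated that 182 patients need to be included".
- Multiplying by 1.2 instead gives 87.6 per group, or about 175 in total, which does not match. The total therefore allows for a true 20% loss: 0.8 × 91 = 72.8 evaluable patients per group.

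**Precision by formula.** Work in SD units with 72.8 patients per group at day 7. The correlation r between baseline and day 7 is not in the documents and is assumed to be 0.4 to 0.6.

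- Unadjusted t test: SE = √(2/72.8) = 0.166.
- ANCOVA on baseline: SE = 0.166 × √(1 − r²), which is 0.152 at r = 0.4 and 0.133 at r = 0.6.
- Equivalent gain in patients: 1/(1 − r²) = 1.19 to 1.56.

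**Precision and bias by simulation.** There were 91 patients per arm and 3,000 trials per setting. All of the following are assumed:

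- SD 1, with a true difference of 0.25 SD at 72 hours and 0.5 SD at day 7.
- Adjacent-visit correlations of 0.5 or 0.7, with baseline to day 7 at 0.4 or 0.6 respectively.
- About 20% lost before day 7, with 25%, 50% or 100% of that loss after the 72-hour visit.

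The mixed model was represented by its likelihood estimate for monotone missing data: a regression of the 72-hour value on arm and baseline, combined with a regression of the day-7 value on arm, baseline and 72-hour value.

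Under random loss the standard errors were:

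- t test: 0.163 to 0.169.
- ANCOVA: 0.151 to 0.153 at the lower correlation, 0.129 to 0.133 at the higher.
- Mixed model: 0.148 to 0.152 and 0.128 to 0.132.

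Setting by setting, the 72-hour value cut the ANCOVA standard error by a further 0.5% to 1.7%.

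Bias in the day-7 difference, in SD:

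| Loss before day 7 (assumed) | t test | ANCOVA | Mixed model |
|---|---|---|---|
| 20%, random | within 0.003 | within 0.003 | within 0.004 |
| 20%, depends on the 72-hour value in the control arm | −0.04 to −0.15 | −0.02 to −0.07 | within 0.005 |
| 20%, depends on the unseen day-7 value in the control arm | −0.09 to −0.22 | −0.06 to −0.19 | −0.05 to −0.16 |
| 5%, depends on the 72-hour value in the control arm | −0.02 to −0.03 | about −0.01 | within 0.003 |

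**The case against.** **A reader might infer that the plan fixes an end-of-treatment test which discards the 72-hour data and drops about 20% of patients.** The document does not say that. Section 2.8 names no time point, so the same tests may also be run at 72 hours. It states no rule for missing values, and such rules may sit in an analysis plan that is not shown. Section 2.4 inflates for shedding and other factors without timing. The remark on unknown reasons for loss follows the 30-day contact, which comes after the main outcomes are measured. It can be answered that inflating to keep 73 evaluable patients per group suggests loss from the efficacy comparison, but that is an inference. What stands is only how the named test works: one value per patient and no baseline.

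**A reader might also infer an inflated error rate.** In a separate simulation under no treatment effect, with about 21% loss and dropout slopes on the 72-hour value that differed by arm, the t test rejected in 10% to 26% of trials. Those slopes are invented, and the top figure needs opposite dropout patterns in the two arms. With slopes of zero in both arms it rejected in 4%. Generating dropout from an observed value also makes the likelihood model unbiased by construction. These rates are not a forecast for this trial. Section 2.5 calls patients and researchers blind, while the Discussion concedes that blinding is not strict, so differential loss is possible but not shown.

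**The t test might be meant for change from baseline.** Section 2.8 does not say so, and it would not close the gap. The standard error of a change-score comparison is √(4(1 − r)/72.8), which is 0.182 at r = 0.4 and 0.148 at r = 0.6, against 0.152 and 0.133 for ANCOVA.

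**The model does not touch the effective rate on which the trial is sized.** This is correct. The point concerns the continuous outcomes only.

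**Conclusion.** The point holds as a cheap improvement to a stated method, not as a demonstrated error. For the continuous outcomes, section 2.8 chooses a test that leaves available information unused. At assumed baseline to day-7 correlations of 0.4 to 0.6 and 20% loss, adjustment lowers the standard error from about 0.165 SD to between 0.15 and 0.13 SD. Almost all of this comes from the baseline value.

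The case for the 72-hour value is mainly about bias, and it depends on how loss arises. The model removes the bias if loss before day 7 depends on observed values and reduces it only in part if loss depends on the unseen day-7 value. With random loss there is no bias to remove, and at 5% loss there is little. Since the protocol gives neither the timing nor the mechanism of loss, the precision gain is the firmer ground for the change.

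**What to change.** In section 2.8, replace the between-arm t and rank-sum tests of each continuous outcome with a mixed model for repeated measures. Use baseline value, arm, visit and arm-by-visit as fixed effects, an unstructured covariance, and NT-pro BNP and BNP on the log scale. Letting the baseline slope differ by visit would match the calculation above. Take the end-of-treatment arm difference as the test for that outcome, and report the 72-hour difference as supportive. This gives one test per outcome; it does not settle multiplicity across the four main outcomes.

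First clarify whether the 72 hours in section 2.7 run from the start or the end of treatment, and reconcile this with section 2.5, which mentions evaluation only before and after treatment. If that cannot be settled, use ANCOVA on baseline at end of treatment. It keeps nearly all of the precision gain but only part of the protection against bias.

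The cost is wording and some programming. No new data, visits or patients are needed, the sample size is unchanged, and the MIXED procedure in the named software can fit the model. The downside is a missing-at-random assumption, which cannot be tested and is harder to support if reasons for loss are not recorded. Patients lost before 72 hours still contribute no outcome value. Add a simple sensitivity analysis, for example shifting the expected day-7 values of lost patients by a range of amounts in each arm.

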### Study design

2.5

In this study, through prehospital recruitment, in-hospital inpatients to screen patients who meet the criteria, patients and their families approve the study program and sign the informed consent form. The patients will be randomly assigned to the treatment group and the control group. Among them, the treatment group will receive Shenfu injection (Shenfu injection 40 mL injection + 5% GS 250 mL injection, ivgtt, QD) combined with intravenous drip of sodium nitroprusside (sodium nitroprusside 3 μ g / kg/min), while the control group will only receive intravenous drip of sodium nitroprusside. Patients in both groups will receive the same routine care and drug treatment, such as angiotensin converting enzyme inhibitor/angiotensin II receptor blocker, beta blocker, diuretic, etc. If necessary, the attending physician can adjust the program according to the patient's condition, and all interventions will be recorded in detail for final result analysis. We will set up a special drug manager, and the nurse will be responsible for preparing the medicine and preparing the solution. Therefore, the study is not blind to nurses, but to researchers, patients, and statisticians. All patients will receive an intravenous injection once a week. The health status of each patient is evaluated before and after treatment, including efficacy and safety indicators, and all patients are followed up by telephone for 30 days. Follow-up included cardiovascular events and rehospitalization.

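### The protocol says reasons for loss to follow-up cannot be collected, so losses caused by 30-day events cannot be told from harmless ones

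*Protocol article*

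**What the plan says.** Section 2.7 (Data collection and management) schedules data collection before treatment, at 72 hours and at the end of treatment, then a contact by outpatient visit or telephone thirty days later. The next sentence reads: "The reasons for the loss of follow-up cannot be collected".

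Section 2.5 (Study design) says what the later contact is for: "Follow-up included cardiovascular events and rehospitalization".

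Section 2.4 (Sample size calculation) plans for attrition. It states "The sample size of each group is calculated to be 73" and then "Considering shedding and other factors, the expansion is about 20%, and it is calculated that 182 patients need to be included", with patients "divided into control group (n = 91) and the observation group (n = 91").

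Three other places bear on the point. Section 2.2 lets patients leave at any time. Section 2.6 lists adverse reactions during treatment as an outcome, and does not list 30-day events among the main or secondary outcomes. Section 2.8 gives the tests to be used, none of which draws on the reason for a missing value.

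**The concern.** This is a positive statement about data collection, so it cannot be excused as detail left to a fuller protocol or an analysis plan. An analysis plan written later cannot use reasons that nobody recorded.

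The events sought at thirty days can themselves make a patient unreachable: someone who has died or been readmitted may not answer the telephone or attend the clinic. If such patients are entered only as lost, with no cause, they look the same as patients who moved house or lost interest. The 30-day event rate among those reached may then be too low. A difference between arms in why patients were lost would also go unseen.

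There is a smaller effect during treatment. A patient who stops because of a reaction may have that reaction on record, but nothing would connect it to the withdrawal.

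**Working it through.** **1. Reproduce the planned allowance for loss.** Inputs, all from section 2.4: "the therapeutic efficiency of Western medicine is 72.3%, and the effective rate of traditional Chinese medicine combined with Western medicine is 92.1"%; "set the significance test level α = 0.05, then μ_α_ = 1.96, 1−β = 0.9, μ_β_ = 1.28".

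- Difference: 0.921 − 0.723 = 0.198.
- Variance term: 0.723 × 0.277 + 0.921 × 0.079 = 0.2003 + 0.0728 = 0.2730.
- Per-arm n by the protocol's formula: (3.24 / 0.198)² × 0.2730 = 73.1, stated as 73.
- Inflation as n / (1 − d) with d = 0.20: 73 / 0.8 = 91.25, giving 91 per arm and 182 in total. The alternative n × (1 + d) gives 87.6, or 88 per arm and 176 in total, which does not match.

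So the stated expansion is an allowance for about 20% loss: 91 − 73 = 18 per arm, 18 / 91 = 19.8%, or 36 of 182 patients.

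**2. What unexplained loss does to a 30-day event rate.** Let m of 91 patients in an arm be lost with unknown status, and let e events be seen among the 91 − m who are reached. The rate among all 91 lies between e / 91 (no lost patient had an event) and (e + m) / 91 (all did). The width is m / 91, whatever the observed rate.

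The protocol gives no 30-day event rate, so the observed rates below are assumptions. With m = 18 and 73 patients reached:

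| Assumed observed rate | e | Lower bound | Upper bound |
|---|---|---|---|
| 5% | 3.65 | 4.0% | 23.8% |
| 10% | 7.30 | 8.0% | 27.8% |
| 20% | 14.60 | 16.0% | 35.8% |

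Each band is 19.8 points wide. If the arms had equal observed rates and 18 losses each, the extreme case (all losses events in one arm, none in the other) would move the difference by 19.8 points either way.

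**3. How the band depends on the amount lost.** The share of the allowance that falls at the 30-day contact is not stated. With m = 5 the width is 5 / 91 = 5.5 points; with m = 9 it is 9.9 points; m = 18 is the ceiling.

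**4. What recording would change.** The band comes from unknown outcomes, so writing down refusal or unreachable does not by itself narrow it. It narrows where status is obtained: if 12 of 18 lost patients were traced, the width would fall from 18 / 91 = 19.8 points to 6 / 91 = 6.6 points. For the rest, the reason is the evidence for choosing a scenario less extreme than the bounds.

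**The case against.** The best defence is one of wording and context. The text says reasons *cannot* be collected, which expresses inability and not a decision. In translated prose it may mean only that an unreachable patient cannot be asked, and its position suggests that it concerns the 30-day contact. That reading is possible. But nothing in the article limits the sentence in that way, or names another source for a lost patient's vital status or readmission, and the assistants collecting the data would work from the sentence as printed.

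The other objections limit what may be concluded, and they stand. A reader might infer any of the following, and the document supports none of them:

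- **That side effects leading to withdrawal vanish.** Reactions during treatment are a listed outcome (section 2.6), and data are collected at 72 hours and at the end of treatment (section 2.7). Only the link to the withdrawal is lost.
- **That 20% of patients will be lost at thirty days.** The allowance covers other factors besides dropout, and none of it is assigned to the 30-day contact.
- **That no sensitivity analysis is possible.** Best- and worst-case bounds, tipping-point and delta-adjusted analyses need no recorded reasons. Loss counts can still be compared between arms.
- **That results are biased towards fewer events.** This holds only if losses are enriched for events. The direction of any bias between arms is unknown.
- **That the band rivals the planned effect because both are 19.8 points.** The planned difference is in effective rate, which is a different outcome.
- **That the main results are at risk.** The main and secondary outcomes are due by the end of treatment, so loss at the later contact does not touch them.

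**Conclusion.** The point holds in a limited form and should be corrected. The sentence in section 2.7 works against the stated purpose of the 30-day contact: it gives up the information needed to tell event-related loss from harmless loss, and no later analysis can restore it. The 30-day event rates may be understated, and the reasons for loss cannot be compared between arms.

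The size is at most a 19.8-point band per arm. That assumes the whole planned allowance (18 of 91) is lost at thirty days with status unknown; fewer losses narrow it in proportion. Neither differential loss nor a direction of bias is shown. The harm falls on 30-day events and on the account of why patients left treatment early. The main and secondary outcomes are affected only for patients who leave before the end of treatment.

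**What to change.** Delete the sentence from section 2.7. In its place, state that for every patient who does not complete treatment or the 30-day contact the following are recorded:

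- date of last contact;
- reason, with categories that include death, rehospitalization, adverse reaction, refusal and unreachable;
- vital and readmission status, from the hospital record or a family contact where obtainable.

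Count known deaths from cardiovascular causes and known readmissions as 30-day events, and report the reasons by arm. If the sentence was meant to say only that reasons may sometimes be unobtainable, say that, and keep the requirement to try.

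The cost is one case report form field and a few extra calls or record checks by the assistants who already collect the data. Section 2.5 has patients recruited through the hospital with family agreement, so both sources are realistic. Sample size and treatment do not change. The change should be in place before enrolment, because the information may not be recoverable afterwards.
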